#### Component 1: objective environmental assessment of the upgraded ICU environment

This observational component of the study has been designed to generate a comprehensive quantitative account of the upgraded ICU environment with reference to physical space, sound, acoustics, lighting, temperature, and humidity, and compare with previously collected baseline/control data. The intervention bedspaces will be continuously monitored for the study period, with sound levels (dB/dBA), light levels (lux), temperature (°C), and humidity (%) all being monitored via wireless integrated environmental monitoring sensors (Senseagent LP4-204 Hilbert Sensor). These sensors communicate via a wireless LP4-391 Neumann Gateway, with members of the research team able to download the data from a cloud-based database into an Excel spreadsheet. The evaluation of sound levels will also include audits of the number and type of alarms, with alarm data downloaded from key equipment in ICU, including patient monitors and ventilators.

A detailed acoustic and lighting evaluation will be performed. A specialist acoustic technician will perform digital acoustic testing of the intervention ICU bedspace environment. Photometric measures of the lighting environment will be collected over a 48-h period. Measurements will include indoor vertical and horizontal illuminance (photopic and melanopic), luminance, and reflectance values at both room and patient level. Measures will be collected with unobtrusive, validated, and calibrated instruments, including wearable devices to evaluate the lighting quality and quantity as experienced by patients.

Continuous data, such as sound levels, light levels, temperature, and humidity, will be described using mean and standard deviation and compared to previously collected bedspace data using a one-sample *t*-test. Daytime and night-time data will be evaluated and compared. The number of alarms will be described using their frequency and compared to previously collected data using chi-squared tests.

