## Discussion

Despite emerging evidence of the negative impact the physical and sensory ICU environment can have on patient recovery, this is an area of critical care medicine that is commonly neglected during design of ICUs and development of patient care plans. ICU care plans usually involve setting targets, which may be targets for optimal sedation levels, ventilation settings, or amount of active exercise, but other factors essential for healing and recovery are commonly neglected, such as targets for quality and quantity of sleep overnight.

Similarly, while ICU clinicians prescribe treatments personalised to patient needs, the ICU environment is inflexible and not adapted to individual needs which necessarily change as the patient’s condition changes. With a growing evidence base demonstrating the importance of environmental factors such as natural light (or light that mimic natural light), noise reduction, biophilia (views of/access to nature), music therapy, and family support, and the rapid development of technology, there is now an opportunity to ensure that ICU bedspaces are flexible and dynamic, allowing personalisation of the space and the ability to modify the environment to suit the patient’s needs at the time. The environment can be optimised for individual patients and adjusted to aid recovery and help facilitate healing.

Previous research on environmental factors commonly addresses the outcome rather than the actual problems. For instance, studies have demonstrated that ear plugs and eye masks can help improve sleep in the ICU [44, 45]. However, this is masking rather than addressing the real problem, which is the continuous increase in noise levels in ICU, reported to increase linearly by approximately 0.4 dBA per annum [19]. Current evidence on the impact of environmental change on patient outcome is limited but suggesting that it may produce positive outcomes [29, 46–48].

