To our knowledge, this is the first study to investigate the impact of large environmental upgrades on patient outcomes in the ICU setting. The strengths of this protocol include the rigorous and multi-dimensional evaluation of both patient outcomes and experiences. The group of consumers (former ICU patients and their families) that helped co-design the upgraded ICU bedspaces also provided feedback and essential input into how they felt the bedspaces should be evaluated and therefore the study design, ensuring we are evaluating what is important to ICU patients. Limitations include that the study is conducted at a single site with a specific local context, potentially impacting on generalisability of data. Also, as only two bedspaces have been upgraded, the small number of beds will limit the number of patients we are able to recruit to the study. A prolonged data collection period, with regular interim data analyses, has been chosen for this reason to ensure sufficient data is collected to be able to compare the intervention bedspaces with control bedspaces. Additionally, there were no perfectly matched beds for the case–control sub-study. When the doors are closed, the implementation bedspaces function like a single room; however, the doors are much wider than the other single rooms in the unit making them functionally closer to open-plan bedspaces when the doors are open. Considering all the other single rooms have windows, it was therefore decided that the bedspaces closest in function and design to the implementation bedspaces were the three chosen open-plan and windowless ones. Lastly, during the upgrade of the two bedspaces, there were multiple changes made to the design, function, and technology in the bedspaces. Should the upgraded bedspaces demonstrate improved patient outcomes, it will not be possible to determine which feature(s) of the intervention bedspaces that contribute to these improvements, or their proportion towards contribution.

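### Component 1 summarises decibel readings by their mean and SD, so the reported change in noise can differ, in either direction, from the change in average sound exposure

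*Protocol article*

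**What the plan says.** The section on Component 1 logs "sound levels (dB/dBA), light levels (lux), temperature (°C), and humidity (%) all being monitored via wireless integrated environmental monitoring sensors". Its analysis paragraph handles all four variables in one sentence: "Continuous data, such as sound levels, light levels, temperature, and humidity, will be described using mean and standard deviation", and these are to be "compared to previously collected bedspace data using a one-sample *t*-test". It adds: "Daytime and night-time data will be evaluated and compared".

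No energy-equivalent level, percentile level or conversion from the decibel scale is named. The section also plans alarm audits and a separate test: "A specialist acoustic technician will perform digital acoustic testing of the intervention ICU bedspace environment". The measures for that test are not named.

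Two other places bear on the spread of the readings. Table 1 (Background) lists acoustic-glass doors added to open-plan bedspaces, absorbent surfaces, fewer and repositioned alarms, and sound masking. The limitations paragraph of the Discussion says: "When the doors are closed, the implementation bedspaces function like a single room", and that the beds are closer to open-plan when the doors are open.

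**The concern.** Lux, °C and % are linear scales; the decibel is not. A mean of decibels is the logarithm of the geometric mean of sound energy, so it lies at or below the energy average, and the shortfall grows with the spread of the readings. If two data sets have the same spread, the shortfall cancels when they are compared. If the spreads differ, the difference in means mixes a change in level with a change in variability.

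Here the intervention itself can change variability. A bed that alternates between a closed and an open state has a two-level sound distribution, which a bed without doors lacks. A mean and SD also describe such a distribution poorly: with 45 and 55 dBA for half the time each, the mean of 50 represents neither state.

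Noise reduction is the first target in Table 1, and Component 1 supplies the objective evidence that the beds are quieter. A reader could not recover the change in exposure from a reported difference in mean decibels.

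**Working it through.** **Inputs from the protocol article.** The scale is dB/dBA, the summary is mean and SD, the comparison is with earlier bedspace data, and the upgraded beds have two door states. The plan states no sound level, SD, share of time with doors open or expected difference, so there is no figure to reproduce. All levels below are assumptions.

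**Formulas.**
- Mean of decibels: M = Σ pᵢLᵢ, where pᵢ is the share of time at level Lᵢ.
- Energy average: Leq = 10·log₁₀(Σ pᵢ·10^(Lᵢ/10)).
- For normal readings: Leq − M = (ln 10/20)·SD² ≈ 0.115·SD².

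**Step 1: shortfall within one data set, normal readings.** SD of 3, 4, 5 and 6 dB gives 1.0, 1.8, 2.9 and 4.1 dB.

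**Step 2: shortfall for a two-state bed.**
- 45 dBA closed, 50 open, half the time each: M = 47.5, Leq = 48.2, shortfall 0.7 dB.
- 45 closed, 55 open, half each: M = 50.0, Leq = 52.4, shortfall 2.4 dB.
- 45 closed, 60 open, open 25% of the time: M = 48.8, Leq = 54.4, shortfall 5.6 dB.

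**Step 3: effect on the comparison.** Let the upgraded bed equal the comparator with doors open and be d dB quieter with doors closed, open for a share f of the time. Take the same within-state SD throughout, so that it cancels. The reduction in mean decibels is (1 − f)·d. The reduction in Leq is −10·log₁₀(f + (1 − f)·10^(−d/10)).

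| d (dB) | f | Reduction in mean dB | Reduction in Leq | Excess |
|---|---|---|---|---|
| 8 | 25% | 6.0 | 4.3 | 1.7 |
| 8 | 50% | 4.0 | 2.4 | 1.6 |
| 8 | 75% | 2.0 | 1.0 | 1.0 |
| 10 | 50% | 5.0 | 2.6 | 2.4 |
| 10 | 70% | 3.0 | 1.4 | 1.6 |

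For example, d = 10 and f = 50% gives −10·log₁₀(0.5 + 0.5 × 0.1) = −10·log₁₀(0.55) = 2.6 dB, against 0.5 × 10 = 5.0 dB.

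**Step 4: when the excess vanishes or reverses.** For roughly normal readings the excess is 0.115 × (SD²upgraded − SD²earlier). Equal SDs give 0. An earlier SD of 5 with an upgraded SD of 3 gives 0.115 × (9 − 25) = −1.8 dB, so the difference in means would then understate the reduction in exposure.

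**The case against.** The strongest case against has four parts.

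1. *Arithmetic averaging is inferred.* The article does not use the word, does not say whether each sensor record is already an interval Leq, and condenses a full protocol available on request. This stands as a caution. But mean, SD and t-test applied to downloaded decibel readings have no other natural reading. Averaging interval Leqs arithmetically leaves the same shortfall between intervals whenever a door state outlasts the logging interval. The day/night split does not remove door variation within each period.

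2. *Direction and size are not fixed.* This stands in full. A reader might infer that the upgraded beds will look much quieter than they are and that the noise effect is therefore misstated. The documents do not support that. They give no levels or spreads, and do not say which beds supplied the earlier data in a unit that had both open-plan and isolation beds. Fewer alarm peaks and sound masking could narrow the spread and reverse the sign. A case in which noise appears to fall while exposure does not can be built: 58 dBA open and 45 closed, half each, against a comparator at 55, gives a 3.5 dB lower mean but a 0.2 dB higher Leq. It needs the open upgraded bed to be louder than the comparator, which nothing in the article suggests.

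3. *A mean of decibels is a legitimate description of typical level.* True, and the article does not say that energy exposure is the target. But it does not confine the statistic to typical level either. The alarm audit and the specialist test do not replace the comparison of the continuously logged data.

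4. *Materiality is low.* Component 1 is observational, and the summary is not stated to drive any randomised comparison. The yearly rise that the Discussion cites ("reported to increase linearly by approximately 0.4 dBA per annum") is a background trend, not a threshold for this study. This stands, and limits the weight of the point.

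**Conclusion.** The point holds in a limited form. The plan summarises and tests a logarithmic variable as if it were linear. The resulting difference measures a change in typical level, and can depart from the change in average sound exposure in either direction. The departure is zero with equal spreads and about 1 to 2.5 dB too large a reduction in the door examples (closed state 8 to 10 dB quieter, open 25% to 75% of the time). It is below 1 dB if the two states differ by only 5 dB, and negative if the earlier data are more variable. These sizes rest on assumed levels and on reading the plan's mean as a mean of decibels. The algebra does not depend on them. It is an inexpensive improvement worth making, confined to Component 1; the randomised patient outcomes are untouched.

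**What to change.** Take sound out of the shared sentence on means and SDs and give it its own rule:

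- Use the A-weighted series for both the new and the earlier data.
- Convert readings to energy, average within each bed and each day or night period, and convert back to give LAeq.
- Compute the earlier bedspace data in the same way and compare the period-level LAeq values.
- Report L10, L50 and L90 alongside, to show peaks and background.
- Label any decibel-scale mean as typical level only.

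The cost is a few lines of analysis text and a simple transformation of data already logged. If only means survive from the earlier study, its raw readings must be retrieved. The reported noise reduction may change, in either direction.

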## Design and methods

### Setting

This study will be conducted in a 27-bed adult ICU at a large urban Australian tertiary referral hospital specialising in cardiothoracic surgery and medicine. The ICU originally comprised 21 open-plan bedspaces and six isolation beds in three ‘pods’ of nine beds each, surrounding a central nursing station. Two of the windowless open-plan bedspaces were modified and will serve as the intervention beds; the remaining 25 will function as control beds. The unit admits approximately 1800 patients annually.

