### Recruitment

For an estimated study period of 2 years, all patients randomised to an intervention or control ICU bedspace as part of the RCT or admitted to environmental control bedspaces as part of the case–control study will be screened for suitability to participate in the research study. Suitable patients will be approached by a member of the research team as soon as possible after admission to ICU, in consultation with the treating clinical team. As patient status commonly changes throughout ICU admission, patients may be screened daily until discharge and may be recruited to the study at any time during their admission to ICU if suitable based on the following inclusion/exclusion criteria:

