#### Component 3: sleep quality and quantity

The quality and quantity of participants’ sleep will be measured objectively, using a combination of single forehead sensor electroencephalogram (EEG) and polysomnography, as well as subjectively using validated sleep questionnaires. Sleep studies will only be commenced when the effects of relevant medications are no longer likely to impact on the quality of data collected; therefore, sleep will not be measured on participants that are deeply or moderately sedated (RASS score − 3, − 4, or − 5), or have had a general anaesthetic, drug overdose, or alcohol intoxication in the preceding 24 h. Ventilated and non-ventilated participants will be included.

Sleep will be measured continuously for a 2–4-day study period (dependent on duration of ICU admission) following recruitment using the Somfit single forehead sensor EEG (Compumedics®). This is a recently developed wearable device that is light and comfortable for patients to wear while enabling collection of high-quality EEG signals.

Sleep will be concurrently measured using a gold-standard portable polysomnography (PSG) recorder for a 24-h period. Polysomnography involves the application of sensors and electrodes for the continuous monitoring of physiological variables during sleep. The portable PSG is a small device that is worn as a belt across the patient’s thorax. Ten sensors are attached to the patient: 2 under the chin, 1 next to each eye, and 6 on the scalp. The sensors will measure and monitor muscle tone changes using electromyogram (EMG), eye movements using electrooculogram, and electrical activity in the brain using EEG. The equipment also has an inbuilt oximeter to measure pulse oximetry and can also measure patient body position as well as background light and sound. The equipment also collects electrocardiogram, leg EMG, nasal pressure/thermistor, and ribcage/abdominal movements.

Participants will be asked to complete the validated sleep in the ICU questionnaire and the Morningness-Eveningness Questionnaire before discharge from ICU [36, 37]. The aim of these questionnaires is to establish the patients’ reported quality and quantity of sleep as well as the reasons for sleep disruptions.

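### Component 1 compares sensor readings with earlier data by a one-sample t-test and alarms by chi-squared tests, so its nominal 5% error rate can be far exceeded

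*Protocol article*

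**What the plan says.** The protocol article, under Component 1, sets out an observational account of the upgraded bedspaces, intended to "compare with previously collected baseline/control data". On the measurement schedule it states: "The intervention bedspaces will be continuously monitored for the study period". The Recruitment section gives the duration ("For an estimated study period of 2 years") and the Setting section the number of rooms ("Two of the windowless open-plan bedspaces were modified and will serve as the intervention beds").

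Two tests are named. Continuous measures are summarised by mean and standard deviation and "compared to previously collected bedspace data using a one-sample" t-test, with day and night also evaluated and compared. Alarm numbers are described by frequency and "compared to previously collected data using chi-squared tests".

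The section does not give the size or length of the earlier data, the logging interval, the unit of analysis, the form of the chi-squared test, or an exposure denominator for alarms.

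**The concern.** A one-sample t-test has one source of error: the scatter of the new readings. Here the reference value is the mean of an earlier set of readings and has its own sampling error, which the test drops. The standard error is too small whatever the unit of analysis.

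The second problem depends on that unit. Neighbouring readings from a sensor in one room resemble each other. If raw readings enter the test, the number of independent pieces of information is much smaller than the count the test uses.

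Alarms have a similar difficulty. They accrue over time and cluster within patients and days, so totals vary more than a chi-squared test on frequencies allows. Without an exposure time, totals from periods of different length or occupancy cannot be compared.

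At stake is the statistical support for saying that the environment changed. Objective environmental evaluation is part of the study's stated aim, and a reader of the randomised results will want to know whether the exposure differed as intended.

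**Working it through.** Component 1 states no sample size, power or alpha, so there is no figure of the plan's to reproduce. The check is the actual false-positive rate of a nominal 5% two-sided test (an assumption) when there is no true difference.

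**Formula.** If the true variance of the difference is D times the variance the test uses, the actual rate is 2 × [1 − Φ(1.96/√D)].

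- Baseline estimated from m independent readings, n new readings: true variance s²(1/n + 1/m), variance used s²/n, so D = 1 + n/m.
- Serial correlation ρ between successive readings (first-order autoregressive, as a simple stand-in): D = (1 + ρ)/(1 − ρ).
- Both, with the same ρ in each period: D = (1 + n/m)(1 + ρ)/(1 − ρ).
- Alarm counts with variance-to-mean ratio φ: D = φ.

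**Inputs.** From the article: the two named tests, two bedspaces, and continuous monitoring over about 2 years. Logged hourly, that is 2 × 365 × 24 = 17,520 readings per sensor. The values of n/m, ρ and φ are not given and are varied.

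**One-sample t-test**

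| n/m | ρ | D | False-positive rate |
|---|---|---|---|
| 0.01 | 0 | 1.01 | 5.1% |
| 0.1 | 0 | 1.1 | 6.2% |
| 1 | 0 | 2 | 16.6% |
| 10 | 0 | 11 | 55.5% |
| 0.1 | 0.5 | 3.3 | 28.1% |
| 1 | 0.5 | 6 | 42.4% |
| 10 | 0.5 | 33 | 73.3% |
| 1 | 0.9 | 38 | 75.1% |
| 10 | 0.9 | 209 | 89.2% |

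Worked line: n/m = 1 and ρ = 0.5 give D = 2 × 1.5/0.5 = 6; 1.96/√6 = 0.80; rate 42.4%.

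Simulation (3000 replicates per setting) agrees: 16.0% for n/m = 1, ρ = 0; 54.9% for n/m = 10, ρ = 0; 75.5% for n/m = 1, ρ = 0.9; 89.2% for n/m = 10, ρ = 0.9.

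**Chi-squared test on alarms.** φ = 2 gives 16.6%, φ = 5 gives 38.1%, φ = 10 gives 53.5%. This covers overdispersion only; unequal exposure would add a bias that cannot be sized from the text.

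**Drift.** The Discussion cites ICU noise as "reported to increase linearly by approximately 0.4 dBA per annum". If that held in this unit, readings averaged over 2 years would lie 0.4 × 2/2 = 0.4 dBA above the level at the start, plus 0.4 dBA for each year between the baseline and the start. Later readings would be the higher ones, so the drift would hide part of any noise reduction.

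**The case against.** The strongest reply is that the article does not say raw readings are the unit of analysis. Reducing a sensor series to daily values is ordinary analysis-plan detail, and that plan is not shown. This stands for serial correlation, which is therefore put conditionally. It does not rescue the one-sample test: on daily means the earlier average is still a sample treated as a constant.

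Several stronger readings are tempting, and the documents do not support them:

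- **That component 1 will report significant differences where none exist.** The inflation depends on three quantities that are not given. With a baseline 10 to 100 times larger than the new data and independent units, the rate is only 6.2% to 5.1%.
- **That the chi-squared test also treats the baseline as exact.** Only a goodness-of-fit form would; a two-sample form carries the baseline's error. The form is not stated, so the objection to this test is clustering and exposure.
- **That rising noise could create a false finding of a quieter room.** The cited trend is upward, so it works against such a finding.
- **That concurrent light and sound data from both arms are already in hand.** Component 3 says the polysomnography equipment "can also measure patient body position as well as background light and sound". That is a capability; the text does not say these data will be kept or analysed. The recording also covers only 24 h in consented participants who are not moderately or deeply sedated.

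It is also fair to say that component 1 is observational and includes specialist acoustic testing and calibrated light measurement, so its conclusions do not rest on these p-values alone.

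**Conclusion.** The point holds in a limited form. The one-sample t-test is the wrong test for the comparison described, and an unseen analysis plan that only fixed the unit of analysis would not cure it. Its false-positive rate is about 17% for equal-sized independent periods and about 55% at 10:1. With serial correlation it is higher (42% at ρ = 0.5 and 1:1). For alarms, variance-to-mean ratios of 2 to 10 give about 17% to 54%. All these figures rest on assumed n/m, ρ and φ and on a two-sided 5% level.

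A new series longer than the baseline is plausible, given about 2 years of continuous monitoring, but the documents do not establish it. A reader might infer that the trial's patient results are compromised. They are not directly affected: the randomised comparison is components 3 to 6, and this defect is confined to component 1. It should be fixed, but it is not critical to the trial.

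**What to change.** 1. Replace the one-sample t-test. Reduce the readings to one day and one night summary per bedspace-day, and compare these with the baseline bedspace-days in a two-sample model that allows for bedspace and serial correlation. If its variance model is right, D returns to 1 and the error rate to about 5%.
2. Replace the chi-squared test. Analyse alarms as a rate per occupied bed-day with an overdispersed model, such as negative binomial, clustered on patient. This needs occupied bed-days for both periods.
3. State the size, dates and bedspaces of the baseline data, and the unit of analysis.
4. Report that the historical comparison is open to drift over time, and that the cited 0.4 dBA yearly rise could mask a noise reduction.
5. If polysomnography light and sound are in fact recorded in both arms, report that concurrent contrast as supportive. Making it the main environmental comparison would be a design preference and is not needed to correct the error.

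The cost is revised analysis wording and some programming, provided the baseline data are held at a level that can be summarised by bedspace-day. If only a baseline mean survives, its standard error must be recovered or assumed over a range. No change removes the limit of two upgraded bedspaces, and the model in item 1 does not remove drift.

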2. Improved sound blocking	2. Added doors to open-plan bedspaces with double layer of extra thick acoustic glass and optimal seals
3. Reduced sound production within bedspace	3. Repositioned alarms away from patients’ head, reconfigured and reduced alarm numbers, staff education
4. Improved sound control within bedspace	4. Introduced sound masking and beds with speakers built into them with the ability to link wirelessly to a patient entertainment system, enabling, e.g. individualised music therapy
Light	
1. Optimised lighting specific for two internal and windowless bedspaces	1. Installed a timed and programmed circadian lighting solution able to be modified to patients’ specific needs
Patient connectivity, stimulation, distraction, and engagement	
1. Improved patient stimulation and distraction	1. Patient entertainment system, materials, and colours were carefully chosen to make the space feel less clinical and overwhelming
2. Improved views and connectivity with nature in windowless bedspaces	2. Virtual window and artificial skylight with several available videos that can be selected based on personal preferences
3. Improved connectivity with family and friends	3. Virtual visiting
Staff solutions	
1. Support communication and workflow	1. Updated nurse call system installed, mobile solutions replaced static ones where able (e.g. workstation on wheels), decluttering the bedspaces where able

The aim of the study described in this protocol is to evaluate the impact of the ICU bedspace environmental upgrade on short- and medium-term patient outcomes and operational impact (health economic evaluation, objective environmental evaluation, and staff experience). Findings of the project will be relevant to a range of stakeholders, including health care administrators and providers, clinicians, patients, and their families.

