#### RCT component

The primary study assessing patient outcomes (study components 3–6 described below) is an RCT, in which the two upgraded bedspaces are defined as intervention, while the 25 ‘conventional’ bedspaces serve as control. Eligibility screening, consent, and randomised allocation is a two-step process. All patients admitted to ICU are eligible to be randomised 1:1, except those deemed unsuitable for admission to the intervention bedspaces:

Patients requiring extracorporeal membrane oxygenation, intra-aortic balloon pump, or dialysisPatients admitted to ICU immediately following cardiac surgery, including transplantation

Patients will be randomly assigned to bedspaces as follows:

A random sequence of allocations to intervention and control bedspaces was established by the research coordinator and sealed in numbered, opaque envelopes. ICU floor coordinators and clinical personnel are blinded to this sequence until revealed at randomisation.Randomisation is completed by the ICU floor coordinator/admitting ICU doctor when:At least one intervention and one control bedspace are available at the time a patient is accepted for admission.The patient is eligible for randomisation (see above).The ICU floor coordinator or responsible clinician on duty opens the next envelope in sequence to reveal allocation of the patient to an intervention or control bedspace.The patient is assigned to the allocated bed.Patients will then be assessed for eligibility for participation in the study by a member of the research team (see ‘Recruitment’ section below).

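### Component 1's comparison of in-use sound and alarms with earlier data cannot separate the bedspace upgrade from patient mix, exposure time or calendar period

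*Protocol article*

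**What the plan says.** Under Component 1 of the protocol article, "The intervention bedspaces will be continuously monitored for the study period", with room sensors for sound, light, temperature and humidity. Alarm data are downloaded from equipment that includes patient monitors and ventilators. The comparator is baseline or control data gathered before this study. Continuous measures are compared by a one-sample t-test. For alarms, "The number of alarms will be described using their frequency and compared to previously collected data using chi-squared tests".

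The RCT component section sets who may enter the upgraded beds: "All patients admitted to ICU are eligible to be randomised 1:1, except those deemed unsuitable for admission to the intervention bedspaces". The exceptions are patients needing ECMO, a balloon pump or dialysis, and patients coming straight from cardiac surgery, including transplantation. The Setting section describes the site as a "large urban Australian tertiary referral hospital specialising in cardiothoracic surgery and medicine".

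Table 1 lists alarm changes as part of the upgrade: "Repositioned alarms away from patients’ head, reconfigured and reduced alarm numbers, staff education". The Discussion cites ICU noise as "reported to increase linearly by approximately 0.4 dBA per annum".

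**The concern.** Alarm counts come from equipment attached to patients, and in-use sound depends partly on that equipment, so both depend on who is in the bed. The upgraded beds take a restricted group. The comparator comes from an earlier period, and no matching restriction is described for it. The named tests compare one set of numbers with another and contain no term for case mix, hours of observation or calendar time. The article plans adjustment for diagnosis and severity in the case–control sub-study, but describes none for Component 1.

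What is at stake is the evidence that the upgraded beds were quieter in use. The randomised comparisons of sleep, circadian rhythm, delirium and later outcomes do not depend on Component 1 for their validity. Their interpretation does lean on it, above all if they are null: a reader would then want to know whether the environment really differed between the arms while the trial ran.

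**Working it through.** The article gives no sample size, effect or error rate for Component 1, so there is no stated figure to reproduce. The check is whether the comparison can isolate the upgrade, and how sensitive it is to patient mix.

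**1. The two sides of the comparison.**
- Upgraded beds: study period; four patient groups kept out; sensors run continuously, with no stated limit to occupied hours.
- Earlier data: prior period; beds, patients, occupancy and handling of empty time not stated.
- Test: one-sample t-test or chi-squared, with no covariates and no stated denominator for alarms.

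**2. How large the excluded group might be.** The Setting section says: "The unit admits approximately 1800 patients annually", in 27 beds. The Recruitment section puts patients eligible for randomisation at about 30 per bedspace per year.
- Admissions per bed-year: 1800/27 = 66.7.
- Eligible share: 30/66.7 = 45%, or 30 × 27 = 810 of 1800.
- Not eligible: up to about 55% of admissions. This is an upper bound on the barred share if eligibility also reflects bed availability. It is a share of admissions, not of bed-time.

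**3. Case mix with no true effect.** Let s be the share of earlier bed-time used by barred patients, and r their alarm rate relative to other patients. Both are assumptions. If the upgraded beds hold only the other patients and the upgrade does nothing, the apparent alarm ratio is 1/((1 − s) + s·r).

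| s | r = 1.2 | r = 1.5 | r = 2.0 |
|---|---|---|---|
| 10% | 0.98 | 0.95 | 0.91 |
| 30% | 0.94 | 0.87 | 0.77 |
| 55% | 0.90 | 0.78 | 0.65 |

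The sign depends on r. If barred patients alarmed less often, say r = 0.8 at s = 30%, the ratio would be 1/(0.70 + 0.24) = 1.06. If s = 0 in the earlier data, this bias disappears.

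**4. What the named test would do.** With equal exposure, the chi-squared statistic for two counts is (a − b)²/(a + b).
- 1000 against 909 alarms (ratio 0.909): 91²/1909 = 4.34, p = 0.037.
- 5000 against 4545 alarms, same ratio: 455²/9545 = 21.7, p = 3 × 10⁻⁶.

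A modest case-mix difference can therefore look conclusive. The test also counts every alarm as independent, although alarms cluster within patients.

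**5. Exposure.** With H₁ observed hours now and H₀ before, the ratio of raw counts equals the rate ratio multiplied by H₁/H₀. Without the hours, a count comparison mixes the two. For the room sensors, empty time matters only if occupancy, or the way empty time was handled, differed between the periods.

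**6. Calendar time.** At the cited 0.4 dBA a year, a gap of k years raises expected sound by 0.4k dBA; two years would be 0.8 dBA. This works against the upgrade, so the separate biases need not point the same way.

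**The case against.** The strongest reply is that the bias is inferred, not shown. The earlier data are not described, so they may have come from similar patients. Ventilated patients are not barred, and ventilators and monitors are the only alarm sources named. Limiting the analysis to occupied hours is detail that an article may leave to the full protocol. Reducing alarms is a component of the upgrade, so fewer alarms is partly an intended effect. The technician's acoustic testing and the room photometry do not depend on who is in the bed. Component 1 is labelled observational and lies outside the RCT.

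Most of this stands, and it limits the point. It does not rescue the comparison, because the article itself fixes a historical comparator and tests that cannot adjust, while control beds run at the same time in the same unit.

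Three stronger readings are tempting, and the documents do not support them.
- A reader might infer from 30 eligible out of about 67 admissions per bed that the upgraded beds would stand empty more than half the time, with alarms falling in proportion. The 30 is a unit-wide average and not a cap: some 810 eligible patients a year could fill two beds, and patients admitted to them without randomisation are also expected.
- A reader might infer that sound or alarms would be bound to fall even if the construction had no effect. The earlier case mix is unknown, and the noise drift runs the other way.
- A reader might infer that nothing measures the environment in both arms. Component 4 lists environmental sensors as a data source, and the sleep recorder "can also measure patient body position as well as background light and sound".

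**Conclusion.** The point holds in limited form. As described, the comparison of in-use sound and alarm counts with earlier data cannot attribute a difference to the upgrade, because patient mix, exposure time and calendar period are not accounted for. The size and direction of the bias cannot be determined from the article. The ratios in the table rest on assumed values of s and r and show only that plausible case-mix differences could matter and could reach significance. The conclusion does not extend to the technician's acoustic testing, the room photometry or the randomised patient outcomes. It also does not mean that alarm reduction should be discounted as an effect of the upgrade. This is a worthwhile and cheap improvement, not a threat to the trial's main results.

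**What to change.** In Component 1, make the main in-use comparison concurrent:

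1. Download monitor and ventilator alarm logs for the same calendar period from the beds of patients randomised to control. Compare alarms per occupied patient-hour between the randomised arms, allowing for clustering by patient.
2. Link sensor time stamps to bed occupancy and restrict the sensor summaries to occupied hours.
3. Use the sleep recorder's background light and sound channels in both arms as the concurrent light and sound comparison, and confirm that these channels will be recorded.
4. Keep the comparison with earlier data as descriptive, and state which beds, period and occupancy those data cover.

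The cost is extra log downloads and data linkage. Existing equipment suffices and no more patients are needed. The limitation is that the recorder's light and sound cover only its 24-hour recording in consenting patients, so that comparison is sparser than the fixed sensors would give.
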